### Randomization

After baseline surveys were completed at each matched pair of sites, the Brown Data Manager assigned the sites to either the intervention or control group using a random number generating function in Excel. *See Fig.**1**for the Live Well Viva Bien study flow diagram.*

**Fig. 1 Fig1:**
[figure not shown]
Live Well Viva Bien study flow chart

## Intervention

### Formative research and intervention development

We conducted 10 focus groups (eight exploratory and two confirmatory) at three housing sites with low-income, racially and ethnically diverse residents of subsidized housing complexes (sites not included in the main trial) to inform the development of the intervention. The focus groups lasted one to two hours, were recorded and were led by trained facilitators using standard focus group procedures [67]. Refreshments were served and participants received a $25 gift card.

The first eight exploratory focus groups (four in English and four in Spanish) asked participants about personal and environmental barriers and facilitators associated with purchasing, preparing and consuming more F&V, where they usually shopped and how they felt about the cost, quality and accessibility of F&V in their neighborhoods. The facilitators then explained the proposed intervention and gathered participants’ input and suggestions about each component of the intervention including where and when the markets should be held at the housing complex, the types of produce they would like to see sold at the markets, the best ways to publicize the markets and campaigns, the nutrition education topics that would be most helpful to them, the length and content of the DVDs, types of incentives and/or prizes to offer at the campaigns, and etcetera.

At the end of each focus group, the recordings were transcribed, translated and summarized. The findings were used to inform the development of the recruitment, marketing and intervention materials. After the first draft of the materials were developed, two confirmatory focus groups were held (one in English and one in Spanish) during which participants provided more input into both the content and design of the intervention materials.

A total of 79 participants participated in the formative research: 72 % were female, 39 % were Hispanic/Latino (47 % identified as Dominican). A total of 35 % were White, 27 % were Black/African American, 14 % were mixed race, 48 % were unemployed, 73 % had a high school education or less, and mean age was 59 years.

From these groups we learned that the high cost of F&V, limited access to high quality, affordable F&V in their neighborhoods and limited time to shop and cook were the major barriers to eating more F&V. Thus, specific educational content to address these barriers were included in the intervention materials. Focus group participants expressed interest in learning more about how to prepare F&V, so we created and distributed recipe cards as well as DVD segments on how to prepare F&V and the DVDs used a cooking show format as focus group participants suggested. They also expressed interest in knowing what an appropriate serving size was for F&V as well as the health benefits of eating more F&V; therefore, this information was also included in the intervention materials. When asked about the type of incentives that would most motivate them to participate in the study, they told us Walmart or supermarket gift cards, which is what we chose to use.

Focus group participants gave us the following suggestions for encouraging participation in the FTY markets: ensuring that the produce at the markets was sold at no more than retail price, preferably lower; that it was high quality/fresh; that the markets accepted debit and Electronic Benefits Transfer (EBT) cards; and that residents knew when and where the markets would be held through the use of posters and flyers at frequented locations in the housing complexes. They also gave us a list of the types of F&V they would like to purchase. All of these suggestions were incorporated into the markets.

At the confirmatory focus groups, where we shared drafts of the educational intervention materials and DVDs, participants suggested focusing on one topic per newsletter and using photos instead of cartoon images. For the DVDs, in addition to including cooking show segments, they also suggested sharing the experiences of real people with follow-ups on their progress in subsequent DVDs. They also wanted the DVDs to include multiple short segments rather than a long segment, so they could easily skip from one segment to another. We implemented all of these suggestions in the development of the intervention materials.

### Intervention framework

This multicomponent intervention is based on a social ecological model, which offers a conceptual framework that recognizes that behavior is affected by multiple levels of influence and that an intervention will be most effective when it targets changes in multiple levels or domains [68–70]. The multi-level LWVB intervention operates within the intrapersonal/individual, interpersonal (social), and environmental domains.

The FTY markets focus on changing the physical food environment by increasing access and availability to fresh F&V. The motivational/educational components of the FTY intervention focus on individual and interpersonal factors by enhancing opportunities for social support and networking, increasing opportunities for participants to role model eating F&V and changing perceived norms to support increased consumption of F&V. The intervention also aims to change the informational environment of the housing site by providing regular communication channels through which educational information about healthy eating is distributed, thereby increasing the awareness of the importance and the benefits of eating F&V. The educational materials also aim to change participants’ personal determinants including increasing knowledge, attitudes, skills, self-efficacy, readiness to change, positive outcome expectancies/perceived benefits, taste perceptions, and perceived social support, while decreasing perceived barriers to eating more F&V.

The theoretical framework for the LWVB intervention is the Social Cognitive Theory (SCT), which defines behavior as a triadic, dynamic, and reciprocal interaction of personal factors, behavior and the environment [71–73]. Based on SCT, behavior change is facilitated if the individual believes change is possible, has an opportunity to develop and practice new skills, and receives support from the environment. Reciprocal determinism explains the interaction between personal factors, behavior and the environment. Behavior changes induced by changes in the individual and in the environment are more likely to be effective and sustained. Thus, the FTY intervention specifically targets changes in personal determinants and interpersonal determinants as well as the availability of and access to F&V in the environment. Both the DVDs and the newsletters include testimonials from target audience members discussing benefits that they gained from eating more F&V to improve outcome expectatations/perceived benefits. The newsletters and DVDs provide ideas on how to overcome barriers such as cost, lack of time, lack of social support, lack of cooking skills, etcetera . Role modeling of success stories in newsletters and testimonials in DVDs aims to increase self-efficacy. Moreover, the campaigns incorporate goal-setting, feedback and self regulation techniques such as self-monitoring and problem-solving around barriers. This intervention addresses external/environmental determinants by increasing F&V access and availability directly with the markets. In addition, participants see neighbors purchasing F&V at the markets, which could change perceived norms and social support. The intervention also attempts to change taste perceptions of F&V through the taste-testing demonstrations, recipes and the provision of fresh, high quality F&V. See the Logic Model in Fig. 2.

**Fig. 2 Fig2:**
[figure not shown]
Intervention logic model

### Intervention components

#### ‘Fresh To You’(FTY) discount, fresh fruit and vegetable markets

The intervention sites receive regularly-scheduled, discount, fresh F&V markets for one year. These FTY markets are not farmer’s markets, but rather mobile markets selling both local and non-local produce on a year-round basis at prices at or below local supermarket prices [74]. For the current study, the original plan to bring the markets to each housing complex on a weekly basis changed as we learned through the pilot that most residents only shopped at the markets the first two weeks of the month, consistent with disbursement of Supplemental Nutrition Asssistance Program (SNAP) benefits. Therefore, at the next seven (7) intervention sites, markets were only scheduled during the first two weeks of each month.

Prior to starting the markets, Brown research staff met with the designated site contacts, who helped determine the best times and locations for the markets. On a mutually agreed upon schedule, our produce distributor brings FTY markets carrying between 50 to 70 different produce items, including staples (e.g., potatoes, onions, carrots, celery, tomatoes and bananas); seasonal items (e.g.,clementines in the winter and peaches and blueberries in the summer); culturally desired ethnic produce items (e.g., plaintains, yucca and mangoes) and exotic produce (e.g. Asian pears and purple eggplant) to introduce new F&V to residents.

The majority of the FTY markets at the senior and disabled housing complexes are held indoors as it is difficult for many of these residents to get outside to shop. Markets are also held indoors at family housing complexes during inclement weather. F&V are arranged in bins on the tables in a central location. A check-out station is set up on a separate table that includes a scale for produce weighing and a Point-of-Sale (POS) system that serves as a cash register and a data collection and reporting unit.

Our produce distributor retrofitted a car trailer to serve as an outdoor, ‘mobile fresh F&V market’ (See Additional file 1: Market Photos) and, in good weather, the markets are held outside at the family housing complexes*.* This retrofitted trailer is pulled by a van and brought to each of the intervention group housing sites at pre-determined days and times during the first two weeks of each month on a regularly scheduled basis. The produce items are set up on racks affixed to three sides of the trailer and shoppers enter through the side and rear doors and exit through the rear door. The scale and POS system are set up on a table outside of the rear door of the trailer and shoppers pay for their produce here. FTY markets accept cash, debit/credit cards and EBT cards (SNAP benefits). Each market lasts two hours and the produce is sold at or below retail price. On average, FTY prices are 15 % to 25 % lower than local retail supermarket prices.

Brown University research staff, with the help of a graphic designer, created a logo for the FTY markets, which is used on all promotional materials. Signs, posters, doorhangers and flyers are used to advertise the markets. In addition, the Resident Assistant at each site and Brown research staff often circulate throughout the housing complex on market days to encourage residents to come to the markets.

The FTY intervention at each site begins with a highly-publicized ‘Kick-Off’ event, which includes the first FTY market, chef-run cooking demonstrations and taste-testing events, along with recipes and detailed information about the upcoming intervention activities. Brown research staff also recruit residents into the first, six-week campaign at the Kick-Off events.

#### Motivational/Educational intervention

Intervention materials are delivered to residents of each housing complex before the first market is held. Each resident household in the intervention housing complex receives a large, reusable shopping bag with the ‘Fresh To You’ logo on it that contains a binder with the following materials: a ‘Welcome Page’, which provides an overview of the intervention, the first month’s newsletter, three DVDs, 48 recipe cards and enough three-hole binder sleeves to store the remaining newsletters they will receive. All materials are provided in English and Spanish. A description of each of the motivational/educational intervention components follows.

#### Campaigns

The intervention includes two educational/motivational campaigns: the first campaign, *‘Just Add 2’*, begins at the Kick-Off event at each site and the second campaign, entitled *‘Color Your Plate’*, is held approximately one month after the six-month follow-up surveys are completed at each site. Both campaigns include full-color campaign booklets with goal-setting activities, educational and motivational content, and F&V trackers that ask participants to record the number of F&V they eat each week. These booklets are worded at a 5^th^ grade reading level. Participants are instructed to read one section of the booklet and to complete the weekly activities included in that section. At the end of the week, participants are asked to deposit their weekly trackers into a raffle box kept at each site. A midpoint event and a final event are also held as part of the campaigns with chef-led cooking demonstrations and taste-testing events (see below). At these events, Brown research staff pull several participants’ trackers out of the raffle box and distribute prizes (blenders, microwaves, woks, crock pots, etc.) to the winners. Approximately $500 in incentive prizes are given away at each site. The campaigns are designed to be ‘self-directed’; however, Brown research staff attend the FTY markets to answer any questions.

*‘Just Add 2’,* the first, six-week kick-off campaign, was designed to increase participants’ F&V consumption by two servings by the end. Participants receive a full-color, campaign booklet, which includes: a description of the campaign; instructions; a table of recommended daily F&V intake (in cups) by age, gender and activity level; photos depicting what a one-cup serving looks like for different F&V; a goal-setting form; the weekly F&V tracker as well as motivational and informational, tips and interactive weekly activities. The weekly chapters and activities are as follows: 1: Overcoming Common Roadblocks; 2: Fruits &Vegetables with Meals and Snacks; 3: Fruits &Vegetables on the Go; 4: Shopping for Fruits &Vegetables; 6: Try Something New and 7: Staying on Track.

*‘Color Your Plate’,* the second, six-week campaign, is focused on increasing the variety of F&V that participants eat. Campaign participants receive a colorful campaign booklet that includes a F&V tracker as well as educational and motivational content for each of the six weeks. Each week focuses on a specific color F&V; the last week focused on variety. The weekly chapters are: 1. Red; 2. Yellow and Orange; 3. Green; 4. Blue and Purple; 5. White and Brown; and 6. Overall Variety. Each week’s section includes a table listing the F&V of the color for that week, along with information on how to choose and store each F&V and when they are in season. Columns are also included on the table for participants to check and indicate whether they like or dislike each F&V and whether they have ever tried it. Each weekly section also includes a daily chart where participants can record how many F&V of that color they eat each day of the week. Then, at the end of the week, participants are asked to add up the numbers in this chart and write the total number on the weekly F&V tracker, which they deposit into the raffle box for prize drawings. Each section also includes tips for how to eat more of that color F&V during the week and the associated health benefits of those F&V.

#### Videos/DVDs

Three, 20-min DVDs were created to support and encourage residents in the intervention group to increase their F&V intake. Each DVD includes a menu so participants can easily navigate to specific segments. The first DVD includes information about the FTY markets; cooking demonstrations showing how to prepare healthy meals for less than $6.00; success stories about real people and health benefits associated with eating more F&V. The second DVD includes guidance and a cooking demonstration regarding how to plan quick, healthy meals; additional success stories about real people; information regarding how to save money while eating healthy; how to involve family members in healthy eating; how to find time to eat healthy, as well as a feature on preparing jicama, yucca, leeks, and mangoes. The third DVD includes another cooking demonstration; more examples of how to prepare quick, inexpensive, healthy meals; additional success stories about real people; and a feature on preparing spaghetti squash and starfruit.

#### Monthly newsletters

A two-page, full-color monthly newsletter is delivered to the door of each intervention housing complex resident on the first day of each month either by the onsite Resident Assistant or Brown research staff. Each newsletter highlights a particular F&V in season that month as well as key nutrients and health benefits associated with the featured F&V and information on how to choose and store them. The newsletters also include a section that lists other F&V in season that month and a section explaining how to save time and money when buying and preparing these F&V. The back side of each newsletter includes a recipe for the F&V of the month with colorful photos of the completed recipe.

#### Recipe cards

A total of 48 recipe cards were created that correlate with the cooking demonstrations on the DVDs (described above). These recipes were chosen because they were easy-to-follow, healthy, relatively quick to prepare, inexpensive and included culturally desired ethnic foods such as jicama, yucca, plantains and mangoes. All recipes were provided in both English and Spanish.

#### Cooking demonstrations

A trained chef visited the housing sites six times during the one year intervention period before, during and after the campaigns on the day of a market. She presented half-hour long cooking demonstrations that featured at least one fruit or vegetable, explaining to participants how to prepare it. One of our bilingual staff translated for the Spanish-speaking participants. All participants received a copy of the recipe that was demonstrated. All of the F&V in the recipes were available at that day’s market.

### Comparison/control intervention

Brown University contracted with the Greater Providence YMCA to provide a physical activity and stress reduction intervention at the 7 housing complexes in the comparison group. Two, six-week campaigns were developed jointly by the Brown study team and YMCA staff. These campaigns follow the same format as the intervention group campaigns and are provided during the same time periods as those at the intervention sites. Campaign participants also receive a free, 6-week membership to the YMCA.

#### ‘Take 10!’ Campaign

The first comparison group campaign is ‘*Take 10!*’ which aims to increase participants’ daily physical activity by 10 min per day until participants reach the goal of at least 30–60 min per day. Participants are given a campaign booklet that includes six weekly sections focused on a particular goal and included: educational and motivational content, a goal setting and action step form, tips and suggestions for how to achieve that goal and the benefits associated with reaching the goal. The focus areas for each week are: 1. Move More, Sit Less; 2. Strength Training; 3. Increase Flexibility; 4. Walk More; 5. Add Intensity; and 6. Make Simple Changes.

Each week, participants are encouraged to read through that week’s section of the booklet, review their weekly goals and do the activities included in that week’s ‘Action Plan’ along with the bonus point activity. At the end of each day, participants are asked to write down the total number of minutes they spent being physically active on the Activity Tracking Sheet. Then, at the end of each week, they are asked to fill out the Weekly Raffle Form and return it in order to earn points toward the incentive prizes. For every ten points earned, participants receive a raffle ticket that is entered into a drawing at the midpoint and final events. Approximately $500 in incentive prizes was given away at each site.

#### ‘Stress Less’ Campaign

The second comparison group campaign was ‘*Stress Less’*, which aims to help participants reduce the amount of stress that they experience by adding stress reduction activities into their daily routines. Campaign participants are given a booklet that includes six weekly sections focused on a particular stress reduction technique. Each section includes: educational and motivational content, a goal setting and action step form, tips and suggestions for how to achieve that goal and the benefits associated with reaching the goal. The focus areas for each week are: 1. Muscle Relaxation and Tension Release; 2. Visualization; 3. Adequate Sleep; 4. Mindfulness and Meditation; 5. Time Management for Stress Reduction; and 6. Music for Relaxation. Each time the participants tries one of the recommendations, they record it on their Activity Tracking Sheet along with how they feel about the techniques. Then, at the end of the week, they are asked to turn in a completed Weekly Raffle form to receive points for each activity they tried and receive raffle tickets for incentive prizes. Raffle tickets are drawn at the midpoint and final events with approximately $500 in incentive prizes given away at each site.

## Process evaluation

Research staff collect and compile attendance counts for each of the campaign events at each site. Detailed FTY market sales data, including total sales, number of shoppers, items purchased and tender types are captured by the FTY POS cashiering system. Research staff record the number of participants who participate in the campaigns and other activities. The 6- and 12-month follow-up surveys include questions about participation in each component of the intervention including frequency of shopping at the FTY markets; perceptions of prices, quality and availability of F&V; participation in, or reasons for not participating in, each campaign; helpfulness of each campaign; participation in, and usefulness of, the cooking demonstration and taste testing events; and the use and usefulness of the recipes, newsletters, and DVDs. Participants are also asked about participant and family changes in shopping behaviors and F&V intake behaviors as a result of the markets. The follow-up surveys also include open-ended questions that ask participants about what they learned and the behavioral changes that they made as a result of the intervention as well as suggestions for how the intervention could be improved.

## Evaluation measures

### Primary outcome measure

The primary outcome is F&V intake, which is measured using two validated instruments: a Two-Item Cup F&V intake screener, [75] and the 18 item National Cancer Institute (NCI) Eating at America’s Table All Day Screener [76]. The two-item measure consists of two questions: “About how many cups of fruit (including 100 % pure fruit juice) do you eat or drink each day?” and, “About how many cups of vegetables (including 100 % vegetable juice) do you eat or drink each day?” Each question includes a description of the amount of F&V in one cup to aid participants in choosing their portion size. Portion size options range from none to 4 cups or more.

The NCI All Day Screener queries foods consumed over the past month. Participants are asked to think about the F&V they usually ate last month and to report the frequency (from never to 5 or more times per day) and serving size (from less than ½ cup to more than 1 ½ cups) for each F&V. Questions are asked about 100 % fruit juice, fruit, salad, french fries or fried potatoes, other white potatoes, cooked beans, other vegetables, tomato sauce, vegetable soup and mixtures that include vegetables. To calculate F&V intake, the response options are standarized to a daily cup serving by multiplying the frequency of consumption by the portion size. The total consumption of F&V is calculated by summing the products of each food group. The responses to the frequency questions are recoded to daily averages based on standard NCI methods [76].

In addition to these two measures, F&V practices are assessed in a series of eleven F&V habits questions adapted from previous questionnaires [51, 77, 78]. These questions include how often in the past few months they: ate fruit at breakfast; added vegetables to breakfast dishes; ate more than one type of fruit per day; ate more than one type of vegetable per day; ate a lettuce-based salad or vegetable at lunch; ate fruit at lunch; eat a lettuce-based salad or vegetable at dinner; ate two or more different vegetables or a vegetable and a salad at dinner; added vegetables to other foods or dishes; ate fruit or vegetables as a snack in-between meals; and ate just fruit as dessert instead of a rich dessert. All questions have five levels of response (always, often, sometimes, rarely or never). The sum of all responses is taken to get the total Fruit and Vegetable Habits Questionnaire score. All items are scored so that higher scores are indicative of higher F&V intake behaviors.

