**Methods/Design:**

One housing complex served as a pilot site for the intervention group and the remaining 14 demographically-matched sites were randomized into either the intervention or control group. The intervention group received bimonthly, discount, mobile, fresh F&V markets in conjunction with a nutrition education intervention (two F&V campaigns, newsletters, DVDs and cooking demonstrations) for 12 months. The control group received physical activity and stress reduction interventions. Outcome measures include F&V intake (measured by two validated F&V screeners at baseline, six-month and twelve-months) along with potential psychosocial mediating variables. Extensive quantitative and qualitative process evaluation was also conducted throughout the study.

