## Methods

### Overview of study design

All study activities occur at housing sites in Providence County, Rhode Island. Pre-intervention focus groups were conducted with housing complex residents (from non-study sites) to inform intervention development. A total of 15 subsidized housing complexes were recruited into the evaluation cohort. One smaller housing complex served as a pilot site for the intervention group and the remaining fourteen demographically-matched sites were randomized into either the intervention or control group. Adult residents from each housing site were recruited for the evaluation cohort prior to randomization. The multicomponent intervention lasts one year and includes baseline, 6 and 12 month follow-up surveys as well as extensive quantitative and qualitative process evaluation throughout the course of the study. Participants are given a $30 gift card incentive upon completion of each of the three surveys ($90 total). All study protocols were approved by the Brown University Institutional Review Board and all participants provided verbal informed consent. A detailed description of the intervention and evaluation follows.

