### Data analysis

To evaluate potential differences between groups that may have occured by chance in the random assignment process, demographics will be assessed by group using chi squared tests for categorical data and analysis of variance for continuous data. Also, group differences in baseline values for outcomes and mediators will be assessed using ANOVA models. To assess characteristics of the baseline F&V intake and mediators, outcomes and mediator variables will be assessed by demographic categories using ANOVA models. To examine F&V intake, mixed-model analysis of variance using SAS PROC MIXED will be used to account for a potential cluster effect within each housing site. All analyses will be performed using SAS version 9.4 (SAS Institute, Cary, NC).

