### Sample size considerations

The original sample size projections showed that ending the study with 75 participants in each of 16 housing complex sites (8 sites per condition) using reasonable estimates of the intraclass correlation (0.01) and Standard Deviation 2.5 (based on our previous studies), we would be able to detect an effect size of 0.50 cups (based on F&V Screener change scores) between experimental groups with 80 % power. We originally planned to recruit 16 sites but dropped our sample size slightly (7 sites in each condition and 1 pilot site = 15 sites) because of large budget cuts from NCI at the beginning of the funding period. We anticipated retention at 75 % or greater of the original sample so aimed to enroll an average of at least 107 participants at each of the 15 housing sites.

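### The primary outcome rests on two unranked instruments at two follow-up times, so the text does not control the false-positive rate of the primary claim

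*Protocol article*

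**What the plan says.** Under Primary outcome measure, the protocol article defines one primary construct and gives it two tools: "The primary outcome is F&V intake, which is measured using two validated instruments: a Two-Item Cup F&V intake screener" "and the 18 item National Cancer Institute (NCI) Eating at America’s Table All Day Screener". Neither is ranked above the other.

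The abstract (Methods/Design) has intake "measured by two validated F&V screeners at baseline, six-month and twelve-months", and Overview of study design confirms that the plan "includes baseline, 6 and 12 month follow-up surveys". Neither place says which follow-up time decides.

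The Data analysis section gives one general model: "To examine F&V intake, mixed-model analysis of variance using SAS PROC MIXED will be used to account for a potential cluster effect". It names no instrument, time point or contrast.

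The Sample size considerations section says the planned design could "detect an effect size of 0.50 cups (based on F&V Screener change scores) between experimental groups with 80 % power". It does not say which screener or which time. The abstract calls both tools screeners, so the term does not identify one.

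**The concern.** Naming the primary endpoint is a protocol task. This article takes it on, with a headed section, scoring details and a power statement, but leaves the endpoint ambiguous. Up to four comparisons could be presented as the primary result: two instruments, each at 6 and at 12 months.

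The two tools can disagree. Both aim at usual daily cups, but one asks two global questions, each with a top answer of four cups or more. The other covers the past month and sums frequency times portion over ten food groups, including fried potatoes and other white potatoes. A resident who replaces potatoes with other vegetables may show no gain on the summed total. The same resident may show a gain on the global questions if he or she does not think of potatoes as vegetables. The article does not say what the trial would conclude in that case.

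The stakes are substantial. The Discussion presents a positive result as the first randomized evidence for such markets and as support for funding them.

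**Working it through.** **Inputs from the article.** Two instruments; follow-up at 6 and 12 months; 0.50 cups; SD 2.5; intraclass correlation 0.01; 75 completers at each of 16 sites (8 per arm), later 7 randomized sites per arm.

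**Assumptions, not in the article.** Each test is two-sided at 0.05. The correlation r between test statistics ranges from 0 to 0.9. The eleven-item habits score is not counted, because the article presents it as additional to the two instruments.

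**Step 1: the plan's own power figure.**
- Design effect: 1 + (75 − 1) × 0.01 = 1.74.
- Effective n per arm: 8 × 75 / 1.74 = 344.8.
- SE = 2.5 × √(2 / 344.8) = 0.190.
- 0.50 / 0.1904 = 2.626, and 2.626 − 1.960 = 0.666, so power is 74.7 % (two-sided, normal approximation).

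The stated 80 % is not reproduced this way. A two-sided t-test with 14 df gives 68.6 %. A one-sided 5 % t-test with 14 df gives 80.3 %, but the article states no sidedness. None of these calculations shows which screener the SD belongs to.

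**Step 2: false-positive rate if any one result may carry the claim.**
- Independent tests: 1 − 0.95² = 9.75 % for two, and 1 − 0.95⁴ = 18.5 % for four.
- Correlated tests: P(at least one |Z| > 1.96) for multivariate normal Z with common correlation r, by simulation with 2,000,000 draws.

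| r | two instruments, one time | two instruments, two times |
|---|---|---|
| 0 | 9.75 % | 18.5 % |
| 0.3 | 9.5 % | 17.4 % |
| 0.5 | 9.1 % | 15.6 % |
| 0.7 | 8.4 % | 13.1 % |
| 0.9 | 7.0 % | 9.4 % |

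Letting the between-instrument and between-time correlations vary separately over 0.3 to 0.9 gives 9.8–17.7 % for four tests, inside the same range.

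**Step 3: rules that hold the rate.**
- One named instrument and time: 5 %.
- Both instruments required: at most 5 %, because joint significance cannot be more likely than significance on one alone.
- Alpha divided over the tests: at most 5 %.

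**Step 4: power cost of keeping both, same normal approximation.**
- 16-site inputs at alpha 0.025: 2.626 − 2.241 = 0.385, so 65.0 %, against 74.7 % at 0.05. Dividing over four tests (0.0125 each) gives 55.1 %.
- 7 sites per arm with 75 completers: 69.0 % at 0.05 and 58.5 % at 0.025.
- Holm tests the smaller p-value at 0.025 and the other at 0.05 only if the first is rejected. Power for a given instrument therefore lies between its 0.025 and 0.05 values.

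**The case against.** A reader might infer that the plan, followed as written, produces a false-positive rate above 5 %. The article does not support this. It states no alpha and no rule that significance on any one measure counts as success, so the rate is undefined. The percentages above also depend on correlations that the article does not give.

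The four-test range is a worst case. A mixed model could yield a single group-by-time test per instrument. The sample size section counts participants at the end of the study, and the intervention runs for 12 months, so 12 months is the more natural deciding time, although the text never says so. On that reading only the two-test range applies.

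Multiplicity rules and exact model contrasts are commonly left to an analysis plan that is not shown here, so their absence is no finding. That objection stands, but it does not reach the core. The article itself makes two unranked instruments primary and powers the trial on one of them without saying which.

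A reader might also infer that the NCI screener is the natural primary because it is more detailed. No section favours it, and choosing it could select a tool on which the power assumption was not based. It would also be too strong to say that the tools measure different things: both estimate daily cups, and both have open-ended top categories.

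**Conclusion.** The point holds in this form: the primary outcome has two unranked instruments and two follow-up times with no deciding measure named, and the sample size does not settle the choice. The text therefore does not control the false-positive rate of the primary claim.

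If any one result at two-sided 0.05 may carry the claim, the rate is about 7–10 % with both instruments at 12 months, and about 9–19 % with both times in play. Both ranges rest on the assumed alpha, the assumed any-one-counts rule and assumed correlations from 0.9 to 0. An unseen analysis plan may already resolve the matter. The point should be corrected, since the remedy is small and needs no new data.

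**What to change.** Before outcomes are examined by arm, name one instrument at 12 months, the end of the intervention, as the primary endpoint. It should be the instrument on which the 0.50-cup and SD 2.5 assumption was based; the investigators can identify it from the previous studies they cite for the SD. State it in both the outcome and sample size sections. Make the other instrument and all 6-month values secondary.

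If both instruments are to stay primary, apply Holm across the two at 12 months and restate the power for each, with an SD and effect suited to that instrument.

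**Cost.** A sentence or two of text and no change to data collection. With a single primary, the other instrument can no longer carry the primary claim alone. With Holm, some power is lost: down to about 65 % from about 75 % for the 16-site inputs. The timing condition matters because site recruitment and randomization are already described in the past tense. A choice made after seeing results by arm would not protect the error rate.
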